#### Defining cases of pDCD

We will define cases based, in part, on the 2011 European Academy of Childhood Disability (EACD) Guidelines for Identification of Children with DCD [30], which require: (1) a score at or below the 16^th^ percentile on a standardized measure of motor impairment (M-ABC-2) [31]; (2) evidence of impact on daily function; (3) IQ score above 70 (KBIT-2) [32]; (4) absence of any medical condition affecting motor functioning (parent reported). In addition, we have also decided to exclude children whose birth weight is less than 1500 grams, as children with very low birth weight are apt to present with a variety of co-morbid health problems that may affect motor coordination. The EACD guidelines also recommend repeated measurement of motor function in children under 6 years of age to ensure valid and reliable identification of children with DCD, which we will also do.

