### Measurements

#### Motor coordination

A standardized motor coordination assessment is conducted in order to identify children with pDCD. We are using the Movement Assessment Battery for Children 2^nd^ Edition (M-ABC-2), the most widely used assessment for the identification of DCD [26, 33, 34]. The M-ABC-2 is an individually administered standardized test which includes 8 motor tasks within 3 categories: Manual Dexterity; Aiming & Catching; and Balance (static and dynamic). Raw scores on these items are converted into standard scores based on the child’s age, and then converted into an overall percentile. Test-retest reliability and standard of error of measurement for the total test scores have been reported to be 0.80 and 1.34, respectively [31]. Studies have shown that the M-ABC-2 is a reliable and valid tool for the assessment of movement difficulties, even in very young children (4 to 6 years of age) [31].

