### Study protocol

#### Baseline testing – Phase 1

All eligible children are assessed in our laboratory to complete Phase 1 of baseline testing. At the baseline visit, parents complete all questionnaires and a semi-structured interview concerning the child’s ability to perform daily activities. The remainder of Phase 1 baseline testing includes assessments of motor skills (to determine presence of pDCD), cognitive ability (IQ), body composition, flexibility and standing long jump. Immediately following completion of the motor skill assessment, test results are scored and entered into a computer database. As mentioned previously, all children who score at or below the 16^th^ percentile on the M-ABC-2 as well as a random selection of children scoring above the 16^th^ percentile are invited into the longitudinal phase of the study and continue testing.

#### Baseline testing – Phase 2

For children selected to continue on to Phase 2 (i.e. longitudinal cohort), percent body fat, aerobic fitness, short-term muscle power output and foot structure are also assessed. At the end of Phase 2, an accelerometer to measure physical activity over the following 7 days is given to the child and any interested family members. An accelerometer logbook and 3-day food diary are also sent home with the family.

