### Data analyses

To evaluate the stability of DCD over time, a straightforward descriptive analysis will be conducted. This will identify children whose scores change over time: those in the pDCD baseline group who, at a later assessment score above the 16^th^ percentile on the M-ABC-2 as well as those children in the control group whose measured performance declines to at or below the 16^th^ percentile, will be identified. At study end, children with 2 or more assessments differing from their baseline group assignment will be considered to have experienced substantial variability in motor proficiency. Depending on the numbers affected, they will either be used to form one or more additional groups in the analysis, or the analysis itself will be altered such that we retain baseline groups, but also model motor coordination as a time-varying characteristic.

To examine the association between DCD and fitness and adiposity, longitudinal growth models will be fitted with fixed effects for gender, baseline age, DCD status, ADHD symptoms (as these measures become available), time, and time by DCD. The outcomes will be total body fat, central body fat, aerobic fitness, and anaerobic fitness. First, these will be modeled as continuous, and then dichotomized at age-appropriate thresholds for overweight/obesity and inactivity, and fit additional models using the logistic link function. The time by group interaction will reveal the direction, magnitude, and significance of any divergence over time between the two groups. If we observe such a divergence, we will test whether it is mediated by physical activity by adding this measure to the above models. Finally, we will test the question of precedence using a distributed lag model in which each outcome is regressed on previous and contemporary measures of the predictors. This analysis will be repeated with a 3-group variable for DCD status that will differentiate among children who score at or below the 5^th^, those who score between the 6^th^ and the 16^th^, and those who score above the 16^th^ percentiles. This will allow us to assess whether the severity of motor impairment is associated with increased risk of poor fitness and overweight/obesity, and whether physical activity is a stronger mediator in the severe motor impairment group.

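### Testing severity through two case bands instead of the continuous M-ABC-2 score gives up about a third of the within-case information, so a null severity result would be hard to read

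*Protocol article*

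**What the plan says.** The Data analyses section first sets out growth models comparing pDCD with controls. It then repeats that analysis with three groups: at or below the 5th percentile, "those who score between the 6^th^ and the 16^th^, and those who score above the 16^th^ percentiles". Two questions are put to this variable. One is whether more severe impairment goes with poorer fitness and more overweight. The other is "whether physical activity is a stronger mediator in the severe motor impairment group".

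Three other places bear on the point:

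- **Score scale and error (Motor coordination).** "Raw scores on these items are converted into standard scores" by age before conversion to a percentile, so a continuous standard score already exists for every child. The section also states: "Test-retest reliability and standard of error of measurement for the total test scores have been reported to be 0.80 and 1.34, respectively".
- **Selection (Study protocol, Phase 1).** Those invited into the cohort are "all children who score at or below the 16^th^ percentile on the M-ABC-2 as well as a random selection of children scoring above" that cut.
- **Repeat testing (Defining cases of pDCD; Data analyses).** "The EACD guidelines also recommend repeated measurement of motor function in children under 6 years of age", and the study says it will do so. If enough children change group, the plan will either form extra groups or "retain baseline groups, but also model motor coordination as a time-varying characteristic".

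The article does not say whether the three bands rest on one test or several.

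**The concern.** Severity is a question of degree, and the study measures it on a graded scale. The plan reduces that scale, among cases, to one yes/no split at the 5th percentile. All differences within the severe band and within the milder band are then ignored, and the split is uneven, with the smaller group at the severe end.

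What is at stake is how a null result would be read. If outcome worsens steadily with lower motor scores, the banded comparison has less power to show it than the data allow, and the report could say that severity makes no difference. The mediation question is more exposed still, because it asks whether an indirect effect differs in the smaller band. The Discussion says that the results should guide which interventions these children need, so a false reassurance about severity would have consequences.

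**Working it through.** **Inputs from the article:** reliability 0.80 and SEM 1.34 (Motor coordination); cuts at the 5th and 16th percentiles (Data analyses); 300 pDCD children and about 10% attrition a year (Study design).

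**Assumptions:** normally distributed scores; cases fall in the two bands at population rates (5/16 severe, 11/16 milder); classical measurement error.

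**1. Reproducing the quoted SEM.** The article gives no SD. From SEM = SD × √(1 − r), SD = 1.34/√0.20 = 2.996. An SD of 3 gives back 3 × √0.20 = 1.34, so the two quoted figures agree with each other.

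**2. Information kept by the split.** Work in SD units, with z(0.05) = −1.645, z(0.16) = −0.994, and normal densities there of 0.1031 and 0.2433.

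- Mean of the severe band: −0.1031/0.05 = −2.063.
- Mean of the milder band: (0.1031 − 0.2433)/0.11 = −1.274.
- Separation: 0.788.
- Between-band variance: (5/16)(11/16) × 0.788² = 0.1335.
- Total variance among cases, with a = 0.2433/0.16 = 1.521: 1 + 0.994a − a² = 0.1997.
- Share kept: 0.1335/0.1997 = 0.67.

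Reliability does not enter this ratio. It shows when the true score is the target: at r = 0.80 the squared correlation with the true score among cases is 0.444 for the continuous score and 0.297 for the bands, and 0.297/0.444 = 0.67. At r = 0.75, 0.85 and 0.90 the ratio is again 0.67. With whole standard scores (mean 10 and SD 3 assumed) it is 0.70.

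**3. What that does to power.** For 80% power at two-sided 0.05, the expected test statistic is 1.960 + 0.842 = 2.80. With the bands it falls to 2.80 × √0.67 = 2.29. Power is Φ(2.29 − 1.96) = 0.63.

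**4. Band sizes.** 300 × 5/16 = 94 severe and 300 × 11/16 = 206 milder. After three years at 10% loss a year, 94 × 0.9³ = 68 severe cases remain.

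**5. Measurement error, a separate matter.** Band width is 1.645 − 0.994 = 0.650 SD, or 1.95 points. In SEM units it is 0.650/√0.20 = 1.45. Where the children observed in each band on one test truly lie:

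| Observed band | Definition of true band | Truly ≤5th | Truly milder | Truly >16th |
|---|---|---|---|---|
| Milder | True-score percentiles | 14.5% | 47.4% | 38.1% |
| Milder | Same raw cuts | 7.1% | 45.1% | 47.8% |
| Severe | True-score percentiles | 62.8% | 31.9% | 5.4% |
| Severe | Same raw cuts | 48.5% | 43.0% | 8.5% |

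So about 53–55% of the milder band are misplaced. The correctly placed share depends on the inputs (true-score percentiles unless stated): 43.0% at r = 0.75, 53.0% at r = 0.85, 50–51% under either definition if the recruited sample sits 0.5 SD below the norm, and 58.6% if the mean of two tests is used.

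**6. Would a continuous score cure the error?** No. The bands are 0.79 SD apart on observed scores and 0.63 SD apart on true scores, a ratio of 0.80. The slope of true on observed score among cases is also 0.80. Attenuation is the same either way.

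**The case against.** The strongest reply is that the narrow band and the proposed change are two separate arguments. That is correct. The one-third loss would be the same with an error-free test, and a continuous version of the same score carries the same 0.80 attenuation. The case for the change therefore rests on step 2 alone.

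A reader might infer from the 1.45 SEM width that most children in the milder band do not belong there, or that bands this narrow cannot sort children by severity. The documents support neither.

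- The misplaced share is about half on a single test, and becomes a minority with reliability of 0.85 or with two tests averaged.
- The bands stay in order. Mean true scores are −1.65, −1.02 and +0.23 SD for severe, milder and above the 16th percentile.
- Most misplaced milder children lie truly above the 16th percentile. That concerns the case cut, which the article takes from the EACD guideline, and not the added 5th-percentile split.

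It is also fair to say that the article plans repeat testing and does not tie the bands to one test. How repeats feed into the bands may be left to a fuller plan. But repeat testing does not restore the information lost by banding, and the rule for children who change group concerns the 16th percentile, not the 5th.

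Finally, the three-group analysis repeats the main models, so the primary two-group contrast is untouched, and its retention of the controls is worth preserving. Both points stand. They limit the weight of the finding but do not remove it, since the article names no other test of severity.

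**Conclusion.** The concern holds as a loss of power in a planned follow-on analysis. Among cases, the bands keep about 67% of the linear information in the M-ABC-2 score (70% on whole standard scores), which turns 80% power into about 63%. This rests on normal scores, population rates within the case group, and an effect roughly linear in the score. It does not depend on the test's reliability. If the true relation were a step at the 5th percentile, the bands would lose little.

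The measurement error is real but secondary: on one test at reliability 0.80, about half the milder band is misplaced, and severity contrasts shrink to about 80% of their size under either analysis. The point is worth acting on because the change is nearly free. It does not invalidate the plan or affect the main comparison of pDCD with controls.

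**What to change.** In Data analyses, make the main severity test the M-ABC-2 standard score (not the percentile) as a continuous term among cases. Fit it in the model that keeps the controls through the DCD indicator, with a score-by-time term for each outcome and a score-by-activity term for the mediation question. Add a check for non-linearity across the low tail. Keep the planned three-group analysis as a supporting, descriptive presentation.

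State which assessment or assessments supply the score. Averaging repeats would reduce the measurement error, which the continuous term alone does not.

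The cost is a change of wording, with no new data, since standard scores are already produced. The downsides are a linearity assumption that has to be checked, and a per-point slope that clinicians will find less familiar than named bands.

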#### Testing secondary objectives

As noted above, we will adjust for covariates that may be associated with motor coordination, fitness and relative body weight. For example, we will estimate the models examining body fat and fitness with an index of ADHD obtained from the Conners’. Other covariates we will examine include perceived self-efficacy, diet, SES, maternal gestational diabetes and parental obesity. We will also examine developmentally important characteristics such as birth weight. Specifically, we will test for an association between DCD and low birth weight (1500–2500 g), and conduct a sensitivity analysis. Importantly, we will test for the potential moderating influence of sex on the association between DCD, inactivity, fitness and relative body weight. Specifically, we will repeat the analyses described in the preceding section, including a 3-way interaction (DCD by time by sex) interaction. This will allow us to ascertain if sex impacts these trajectories.

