## Methods/Design

### Study design

The CATCH study is a prospective cohort study with an initial cohort of 600 children aged 4 or 5 years at baseline: 300 with probable DCD (pDCD) and 300 controls. Using the Optimal Design software package [23], we have determined that an analysis with two groups of 300 assessed on 4 occasions will permit the detection of standardized effect size differences of approximately 0.3 with 80 % power and a significance level of 0.05. Taking expected attrition into account (~10 % per year), standardized effect sizes above approximately 0.35 will remain detectable. This means with 600 participants, we will be adequately powered to detect modest effect size differences between our two groups while accounting for loss to follow-up over time. The control group is randomly selected from the children completing the laboratory assessment who do not meet criteria for DCD. Data collection occurs at annual study visits, which include a motor coordination assessment, anthropometric assessments, and non-invasive physical fitness measures. All measures have previously been conducted successfully in this age group [24–26].

Through a parental interview, DCD questionnaire and demographic survey, parents provide additional information about their child’s performance of daily motor activities, demographics, measures of health and risk factors for obesity (adapted from surveys exploring these risk factors) and measures of participation in physical activity [27, 28]. The Hamilton Integrated Research Ethics Board has provided ethical approval for the study*.*

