### Participants

The target age range for participants is 48 months, 0 days to 71 months, 30 days at study entry. Children with a physical disability or diagnosed medical condition that affects motor coordination (e.g. Cerebral Palsy) are excluded from the study. Children with a birth weight lower than 1500 g are also not eligible. These eligibility criteria are necessary in order to rule out medical conditions other than DCD, which may be responsible for poor motor coordination.

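### The only named birth-weight test is low versus not low (1500–2500 g), so a modest graded association with DCD could be missed; a continuous analysis should be added beside it

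*Protocol article*

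**What the plan says.** Testing secondary objectives opens the topic broadly: "We will also examine developmentally important characteristics such as birth weight". The next sentence narrows it to one form: "we will test for an association between DCD and low birth weight (1500–2500 g), and conduct a sensitivity analysis". The content of that sensitivity analysis is not described.

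The range is already truncated from below. The Participants section states: "Children with a birth weight lower than 1500 g are also not eligible". The section on defining cases explains this limit by the co-morbid problems of very-low-birth-weight children. The article gives no explicit reason for the 2500 g boundary.

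The Study design section plans "an initial cohort of 600 children aged 4 or 5 years at baseline: 300 with probable DCD (pDCD) and 300 controls". Its only power statement concerns the comparison of these groups over four occasions: "standardized effect size differences of approximately 0.3 with 80 % power and a significance level of 0.05". No power, expected effect or low-birth-weight rate is given for the birth-weight question.

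**The concern.** Birth weight is a continuous measure. Once children below 1500 g are excluded, the cut sets a small stratum against everyone else and treats a child of 2510 g like one of 4000 g. If the relation with DCD is graded, most of the information lies above the cut and is discarded.

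The Data analyses section treats the outcomes differently: they are modelled as continuous first and dichotomized afterwards. For birth weight only the dichotomy is named. What is at stake is the reading of a null result. A test with limited power against a modest gradient could be taken as evidence that birth weight and DCD are unrelated.

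**Working it through.** **The plan's own figure.** No power is stated for birth weight, so there is nothing to reproduce for this test. The stated 0.3 comes from a four-occasion calculation whose variance components are not printed, so it can be neither reproduced nor called wrong. A single-occasion comparison of two means with 300 per group would detect (1.96 + 0.842) × √(2/300) = 0.229 SD with 80 % power. The attrition step is consistent with three annual losses of 10 %: 0.3 / √(0.9³) = 0.3 / √0.729 = 0.351, against the stated 0.35. Attrition does not matter for birth weight, which is fixed at entry.

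**Inputs.**
- From the Study design section: 300 per group and significance level 0.05. Sidedness is not stated; two-sided is assumed.
- Assumed: normal birth weight, with the pDCD group shifted downwards by d SD. The reference value d = 0.30 is borrowed from the Study design section, where it describes the repeated group comparison and not birth weight.
- Assumed: low-birth-weight share in controls p0 = 6 %, range 3–10 %.

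**Full scale.** Power = Φ(d × √(300/2) − 1.96). At d = 0.30 this is Φ(3.674 − 1.960) = Φ(1.714) = 0.957; the noncentral t gives 0.956.

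**Low/not-low cut.** The share in the pDCD group is p1 = Φ(Φ⁻¹(p0) + d). At p0 = 0.06, p1 = Φ(−1.555 + 0.300) = Φ(−1.255) = 0.105. The pooled proportion is p̄ = 0.0824.
- SE under the null: √(2 × p̄ × (1 − p̄) / 300) = 0.02245
- SE under the alternative: √((p0(1 − p0) + p1(1 − p1)) / 300) = 0.02238
- Power = Φ((0.0448 − 1.96 × 0.02245) / 0.02238) = Φ(0.035) = 0.514

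At this share the cut would need about 591 per group for 80 % power.

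| Shift d (SD) | Full scale | Cut, p0 = 3 % | Cut, p0 = 6 % | Cut, p0 = 10 % |
|---|---|---|---|---|
| 0.20 | 69 % | 18 % | 25 % | 32 % |
| 0.30 | 96 % | 37 % | 51 % | 63 % |
| 0.40 | 99.8 % | 60 % | 78 % | 87.5 % |
| 0.50 | >99.9 % | 81 % | 94 % | 98 % |

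**Check with truncation at 1500 g.** Simulation at d = 0.30 (assumed control mean 3350–3400 g, SD 500–550 g) gives 95–96 % on the full scale. The cut gives 49–51 % when 5–6 % of controls are low, and 39 % when 3.6 % are.

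**Larger sample.** The article does not restrict this test to the 600. If 16 % of screened children are positive (assumed), 300 positives imply 300/0.16 − 300 = 1575 negatives. At d = 0.30 the cut then has 63 %, 77 % and 86 % power for shares of 3, 6 and 10 %, against 99.7 % on the full scale.

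**Other shape.** Suppose only the low-birth-weight share differs, 5 % in controls against 10 % in pDCD, with no shift elsewhere. In simulation the cut has 67 % power and a linear test about 26–28 %. A model with a quadratic term reaches about 37 %. The order reverses.

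**The case against.** The strongest reply is that the band may be the question. Children below 1500 g are excluded because very low birth weight may itself affect motor coordination. Asking whether the adjacent 1500–2500 g group is over-represented in DCD, with a sensitivity analysis, reads naturally as a check next to that eligibility rule. This stands, and it is a reason to keep the contrast and not demote it. It does not answer the broader sentence, which announces that birth weight as such will be examined.

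A second reply is that a condensed article leaves functional form to the full plan, and that nothing here excludes a continuous analysis. The second part is true: the sensitivity analysis is undefined and could contain one. But the form of the test is stated, not left open, and the stated form is the dichotomy.

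A reader might also infer more than the documents support:
- **That a moderate association has an even chance of being missed while the full scale would almost surely find it.** The contrast needs a uniform shift near 0.30 SD, a size range that the Study design section calls modest: "adequately powered to detect modest effect size differences between our two groups". At 0.50 SD the loss is only about 2–19 points, and under a pure threshold effect the cut wins.
- **That birth weight would be dropped from the growth models after a null, or entered there as a low/normal indicator.** The article makes no covariate's inclusion depend on this test and does not say how birth weight would enter.
- **That weights in grams are certainly in hand.** The article does not say how birth weight is recorded; the two limits could be applied from banded answers.

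**Conclusion.** The point holds in a conditional form. The only birth-weight test named is low versus not low, and it is weak against a modest graded association: about 37–63 % power against about 96 %, a loss of roughly 33–59 points. This rests on a uniform normal shift of 0.30 SD, a 3–10 % low-birth-weight share in controls, 300 per group and two-sided 0.05. The shift and the share are assumptions.

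The loss is smaller for larger shifts. If all Phase 1 children are used (assumed 300 against 1575), it falls to about 14–37 points. If risk is confined to children below 2500 g, the planned contrast is the better test. The documents do not say which shape to expect, which is the reason for running both analyses rather than replacing one with the other. This is a minor improvement to a secondary question; the primary growth models are untouched.

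**What to change.** In Testing secondary objectives, keep the 1500–2500 g contrast and the sensitivity analysis. Add a pre-stated analysis with birth weight as a continuous variable, for example a logistic model of pDCD on birth weight per SD or per 500 g, with a spline or quadratic term for curvature. State that both results will be reported, and that a null low-birth-weight contrast alone will not be interpreted as absence of a relation between birth weight and DCD.

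The cost is a sentence or two of text, one extra model and a second secondary test. It requires birth weight recorded as a number and not in bands. If parents report it, values may be rounded, which would blunt the continuous analysis somewhat.
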